**Stakeholders to be sampled in this study**

| Participant (n)                                                                       | Affiliation of stakeholder      | Method of data collection | Rationale and expertise                                                                                                 |
|---------------------------------------------------------------------------------------|---------------------------------|---------------------------|-------------------------------------------------------------------------------------------------------------------------|
| Medical Officer (2)
Clinical Officer (2)
Nurse (2)
Public Health Officer (2) | Primary Health Care Providers   | FGD, IDI                  | Implementors of vaccination during epidemics                                                                            |
| County Health Officials (6)                                                           | Implementers of policy          | FGD, IDI                  | Planners of vaccination during epidemics                                                                                |
| PPB (2), NDA (2)                                                                      | National Regulatory Authorities | IDI                       | Regulatory authorities                                                                                                  |
| Officials (6)                                                                         | Vaccine Manufacturers           | IDI                       | YF vaccine manufacturers                                                                                                |
| Official (2)                                                                          | GAVI, The vaccine Alliance      | IDI                       | Funding of vaccines                                                                                                     |
| Official (2)                                                                          | PATH                            | IDI                       | YF strategic demand forecasting                                                                                         |
| Official (2)                                                                          | SAGE                            | IDI                       | Subject experts                                                                                                         |
| Official (2)                                                                          | WHO                             | IDI                       | Involved with supply of YF vaccine and interactions with manufacturers, Eliminate Yellow Fever Epidemics (EYE) official |
| Researcher/Academic (3)                                                               | Research Institution/University | IDI                       | Subject experts                                                                                                         |

\*PPB - Pharmacy & Poisons Board, Kenya; NDA - National Drug Authority, Uganda; SAGE - WHO Strategic Advisory Group of Experts on Immunization  
IDI - in-depth discussion; FGD - focus group discussion

The framework shown in Figure 1 maps the key stakeholders that are involved and their link to the policy. We will draw our questions and analysis from the stakeholder analysis approach which can be useful to understand actors' perceptions, behavior, intentions, inter-relations and interests in reference to their past, present positions and future potentials. We will conduct about 25 interviews with the different stakeholders. To ensure accuracy of the data and analysis, we will feedback learning to a sub-group of interviewees as a draft report and seek their views on the key findings and interpretations. Depending on initial data and emerging themes, we may sample more stakeholders at each level of the actors.

## 9. SELECTION AND WITHDRAWAL OF STUDY PARTICIPANTS

### 9.1. Description of the population to be studied

The main study will recruit healthy adults living in Kilifi and Mbarara who are willing to participate. The sub-study will recruit healthy children in Kilifi and Mbarara whose parents/guardians are willing to consent their participation in the study.

### 9.2. Inclusion criteria

- Individuals aged  $\geq 18$  - <60 years of age.
  - For the sub-study, children aged between 9 to 12 months.
- HIV status

- HIV negative on serological screening OR
- HIV positive adults on serological testing, and no symptoms suggestive of current clinical immunosuppression and CD 4 count > 200 (for adults) and CD4% > 25% (for children) within the last 6 months.
- Ability to provide informed consent to participate in the study

### 9.3. Exclusion criteria

- Known contraindications to YF vaccination such as allergies to egg protein and chicken products or any component of the vaccine (including gelatin, eggs, eggs products or chicken products), immunodeficiency, known thymus disorder, such as thymoma and myasthenia gravis
- Using corticosteroids or other immunosuppressive therapy
- Thymus disorder, such as thymoma and myasthenia gravis
- Acute febrile disease on the day of vaccination with temperature > 37.5 degrees Celsius is a temporal contraindication.
- Previous YF vaccination
- Previous YF infection as determined from history
- Pregnancy (as determined by a urine test on the proposed day of vaccination) and lactating women
- Planning to migrate out of the study areas before the end of the study follow-up
- Planning to travel to a country requiring YF vaccination certificate within the first year after vaccination.
- Any condition or criteria, including acute or chronic clinically significant abnormality that in the opinion of the investigator might compromise the wellbeing of the volunteer or interfere with the outcome of the study.

### 9.4. Withdrawal criteria

In accordance with the principles of the current revision of the Declaration of Helsinki, a participant has the right to withdraw from the study at any time and for any reason and is not obliged to give his or her reasons for doing so. In addition, the participant may be withdrawn for any of the following reasons:

- Participant non-compliance with study requirements (for example follow-up visits) despite reminders and attempts to make contact
- Participant moves out of the study area and cannot be traced
- A SAE, which requires discontinuation of the study involvement or results in inability to continue to comply with study procedures

### 9.5. Managing withdrawals

The study team will continue to follow up all vaccine recipients, with their agreement, until the end of the study wherever possible. The reason for withdrawal will be recorded in the Case Report Form (CRF) if given. If withdrawal is due to a SAE, appropriate follow-up visits or medical care will be arranged, with the agreement of the participant, until the event has resolved, stabilized or a non-study related causality has been established. Following Good Clinical Practice (GCP) guidelines, data on participants who specifically withdraw their consent for use of their data will not be included in the data analysis. However, participants who withdraw from follow up without withdrawing consent for use of their data will be included.

#### **9.6. Replacing withdrawn participants**

Participants that withdraw from the study or withdraw their consent will not be replaced.

### **10. TREATMENT OF STUDY PARTICIPANTS**

#### **10.1. Treatments**

The investigational product will be one of the four doses of the YF vaccine.

#### **10.2. Identity of Investigational Product**

We will use YF vaccine produced by Institut Pasteur de Dakar, Senegal. The product will be a freeze-dried preparation of live attenuated YF virus, sub-strain 17D-204. One vial format will be provided. It will contain standard full dose of vaccine for administration in 0.5ml per dose. A second vial will be prepared from a standard vial to contain vaccine diluted to approximately 1000 IU/dose for administration in 0.5ml per dose. Fractional volumes of this second vial will be administered as per manufacturer's instructions to achieve the 500 IU and 250 IU doses. A single vaccine batch will be used in this study

#### **10.3. Storage**

YF vaccine will be stored and transported at a temperature ranging between +2°C and +8°C as per manufacturers' instructions. The vaccine is sensitive to light and needs to be protected from sunlight. The vaccine vials and diluent will be transported together. Vaccine will be reconstituted solely with the diluent provided by the manufacturer. The diluent provided with the vaccine needs to be between +2°C and +8°C at the time of reconstitution. For this, diluents need to be placed in the refrigerator at least one day (24h) before its use. Reconstituted YF vaccine is heat labile hence vials will be discarded 6 hours after reconstitution. The specific manufacturer storage and reconstitution instructions indicated in the product insert will be followed.

Temperatures in the cold chain will be monitored regularly through the day to avoid any deviations. Where temperature excursions occur, they will be resolved with the sponsor following the manufacturer's recommendations. The reconstitution and discard hours will be recorded in the vaccine administration form. The YF vaccines are attached with a vaccine vial monitor type 14 (VVM14), which means the vaccines can withstand cumulative exposure to 37°C for up to a period of 14 days and still retain potency.

#### **10.4. Dose selection**

Standard dose of vaccine will be administered in 0.5ml per dose. For the lower doses, a second vial will be prepared from a standard vial, by the manufacturer, to contain vaccine diluted to approximately 1000 IU/dose for administration in 0.5ml per dose. Fractional volumes of this second vial will be administered as per manufacturer's instructions to achieve the 500 IU and 250 IU doses. A single vaccine batch will be used in this study.

#### **10.5. Timing of Doses**

The vaccine will be administered once during the vaccination visit.

#### **10.6. Randomization and Blinding**

Each participant will be randomized to receive one of the four vaccine doses. The allocation will be to one of the four treatment arms per a computer-generated randomization schedule. Randomization will be done by randomization booklets with concealed scratch cards, allocated in order of recruitment and opened on the day of vaccination. These will be prepared by a person outside the study. To minimize vaccine wastage, randomization will be done in block sizes that match with clinic visit days. Allocations will be concealed until a member of the unblinded study team scratches the randomization booklet to reveal the participants' randomization arm.

All participants will receive the same information regarding adverse events. Participants will not be informed of the allocated vaccine. The vaccine will be prepared outside of the view of the participants.

The children will be randomized to either full dose or the lowest non-inferior dose of the vaccine. The vaccine dose to be used will be selected based on the safety and immunogenicity results at day 28 post-vaccination from the adult study. Similar randomization procedures as the adult study will be used. The children will be vaccinated in collaboration with a Ministry of Health EPI clinic for the EPI Measles vaccine.

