### **8.2.3. Randomization / Enrollment**

Participants meeting the inclusion and none of the exclusion criteria above will be enrolled in the study. Vaccination may occur on the day of screening, or deferred to a later day, depending on the timing of screening and vaccination days. Randomization will take place when a volunteer with confirmed eligibility criteria attends for vaccination and completes the enrollment pre-vaccination

assessment successfully. This will include an assessment for acute febrile disease, and a urine pregnancy test for female volunteers.

Children who will have received or scheduled to receive EPI vaccination will be vaccinated 4 weeks after or 4 weeks before the EPI vaccination to allow for AE assessment and avoid any immunological interference.

Each adult participant will be randomized to receive one of the four vaccine doses. Computer-generated randomization codes will be prepared in randomization booklets before recruitment starts by a person outside of the study. Participants will be allocated to one of the four treatment arms as per the computer-generated randomization schedule. To minimize vaccine wastage, randomization will be done in block sizes that match with clinic visit days. Allocations will be concealed until a member of the unblinded study team scratches the randomization booklet to reveal the participants' randomization arm. Participants will not be informed of the allocated vaccine dose. The unblinded team will observe aseptic techniques when drawing up vaccine from vials and the barrel of the syringe masked using tape to avoid observation of the volume. Participants will be told that this is to avoid them becoming aware of the vaccination dose before the end of the trial, as the vaccines will be drawn up into different sized syringes. The vaccine will be administered subcutaneously in the deltoid region of either arm and upper thigh for children <1 year, avoiding broken skin or injuries. It is recommended, but not required, that the injection be administered into the non-dominant arm. The unblinded team will not participate in further assessments or follow-up visits and will not reveal dose allocations to participants or other trial personnel. All other members of the study team will be blinded until data are locked.

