## **8. TRIAL DESIGN**

### **8.1. Overall Study Design and Plan Description**

This will be a parallel group, randomized, controlled, blinded, non-inferiority trial of four different doses of YF vaccine. The study will be conducted at the KEMRI CGMRC in Kilifi, Kenya and at Epicentre in Mbarara, Uganda. Both these sites are already working together in an ongoing study (Clinicaltrials.gov number: NCT02991495).

Adult participants (n=480) will be randomized for vaccination with full standard dose or with 1000, 500 or 250 IU (i.e. 4 arms) with a 1:1:1:1 allocation ratio. Results for the safety and primary outcome of the adult study will then be reviewed by the DSMB, and the lowest non-inferior dose in the adult study selected for assessment in children aged 9 to 12 months (n=420) in comparison to full standard dose (i.e. 2 arms), when co-administered with the EPI Measles vaccine, with a 1:1 allocation ratio. The determination of the non-inferior dose to use in children will be made by the sponsor in discussion with the study DSMB, vaccine manufacturer and relevant stakeholders, and the final decision communicated to the various regulatory authorities as a notification (i.e. SERU, OXTREC and PPB for the Kilifi site, MUST-REC, UNCST and NDA for the Mbarara site).

Adult vaccinees will be followed up for 2 years, and children for 1 year. There will be no gradual age de-escalation on the basis that there are few safety concerns with the full dose of YF vaccines, having been used in millions of children worldwide. The study procedures will be similar across both sites and these are summarized in Table 2.

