#### **10.7. Dispensing Procedures**

The vaccinating nurse and pharmacist will be unblinded to the allocation of the vaccine doses. They shall not disclose the allocations to any of the team members and they will not participate in the follow up the participants post vaccination. The rest of the trial team will be blinded throughout the study and until data are locked.

Study vaccines will be labelled specifically for the study. Vaccines will be reconstituted once the first participant of the day has been randomized to a specific vaccine dose. The pharmacist together with the vaccinating nurse will be responsible for preparation and administration of the vaccines as randomised. They will be responsible for the accompanying documentation.

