#### **10.8. Dose Administration**

The vaccine dose to be administered will be guided by the randomization process. The doses to be evaluated will be the full standard dose, 1000 IU, 500 IU and 250 IU. After reconstitution according to the manufacturer's instructions the full dose and the 1000 IU will each be in a volume of 0.5ml.

For the 500 IU and 250 IU doses, fractional volumes as per instructions from the manufacturer will be administered. Vaccine will be administered subcutaneously. As multi-dose vials will be used, the aliquot number (1,2,3, etc.) will be documented on the CRF. The YF vaccine contains no preservative; hence the repeated manipulation for vaccine reconstitution and withdrawal could lead to a greater risk contamination of the vial contents. The pharmacist and vaccinating nurse will prepare the vaccine using aseptic techniques.

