### 5.3.3 Safety Analysis

Safety outcomes will be assessed in the Safety population (i.e., any participant who was vaccinated) by study cohort for full and lower doses. All adverse events, serious adverse events, or deaths will be summarised as n (%) by study cohort and by study arm, where n is the number of participants that experienced any event post-vaccination and as a percentage of the total safety population within the study arm. All events (AEs, SAEs, and deaths) will also be presented by MedDRA coding (both System Organ Class and Preferred Term), relatedness to study vaccine, and outcome.

The proportion of participants in each study arm reporting any local reaction will be compared using the Chi-squared test and the difference in proportions with 95% confidence intervals will be presented. This will be repeated for systemic reactions.

All SAEs will be described in detail for each participant. The proportion of participants in each study arm reporting at least one SAE will be compared using Chi-squared test or Fisher's exact test, depending on the distributional assumptions.

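### The 500 and 250 IU arms get a smaller injected volume and nothing conceals the syringe at injection, so participant blinding in those arms is not assured and their reported-reaction comparisons are at risk of bias

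*Supplement*

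**What the plan says.** Protocol v1.6, section 8.1, sets the design: "This will be a parallel group, randomized, controlled, blinded, non-inferiority trial of four different doses of YF vaccine". The SAP title also calls the trial blinded.

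Section 10.8 gives the volumes. After reconstitution, "the full dose and the 1000 IU will each be in a volume of 0.5ml". The other two arms differ: "For the 500 IU and 250 IU doses, fractional volumes as per instructions from the manufacturer will be administered". Sections 6, 10.2 and 10.4 explain that these fractions come from the vial diluted to about 1000 IU per 0.5 ml.

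Section 10.6, repeated in SAP 3.3, gives the safeguards for participants. They are not told their allocation, everyone gets the same information about adverse events, and "The vaccine will be prepared outside of the view of the participants". On staff, section 10.7 says: "The vaccinating nurse and pharmacist will be unblinded to the allocation of the vaccine doses". Those two roles take no part in follow-up, and the rest of the team stays blinded until the data are locked.

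Local and systemic events are asked of participants at follow-up visits (protocol 12.5; SAP 4.2.2). SAP 5.3.3 then plans a test: "The proportion of participants in each study arm reporting any local reaction will be compared using the Chi-squared test", with a difference and 95% confidence interval, and the same for systemic reactions.

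**The concern.** Preparing a dose out of sight does not hide it when it is injected. An adult, or a parent with an infant, can see the syringe and how much is in it. The lay summary says the trial compares a full dose with three lower ones, so a small fill carries information.

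The outcome most exposed is the one participants report themselves. Someone who suspects a small dose may report fewer reactions, or may report differently in some other way. The SAP tests these proportions between arms, and safety is among the data reviewed before a dose is taken into children aged 9 to 12 months.

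A second issue exists even with perfect masking. The 500 and 250 IU arms differ from full dose in both IU and injected volume, so a difference in local reactions cannot be assigned to IU alone.

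**Working it through.** **1. Volumes by arm.** The documents give 0.5 ml for two arms and no figure for the others. Assuming volume is proportional to dose drawn from the 1000 IU vial, volume = 0.5 ml × dose / 1000 IU.

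| Arm | Calculation | Volume | Differs in volume from full dose? |
|---|---|---|---|
| Full dose | stated | 0.5 ml | comparator |
| 1000 IU | stated | 0.5 ml | no |
| 500 IU | 0.5 × 500/1000 | 0.25 ml | yes, half |
| 250 IU | 0.5 × 250/1000 | 0.125 ml | yes, a quarter |

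Two of the three adult comparisons with full dose are exposed.

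**2. Number of participants.** Protocol Table 5 has 120 adults per arm: 2 × 120 = 240 of 480 receive a reduced volume. In children it is 210 of 420 if a fractional-volume dose is chosen, and none if 1000 IU is chosen.

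**3. Search for concealment at injection.** In protocol v1.6, section 8.2.2 covers injection site, observation and staff blinding. Section 10.6 covers non-disclosure and preparation. Section 10.7 covers who is unblinded, and section 10.8 covers volumes and aseptic handling. SAP 3.3 repeats 10.6. None mentions a covered barrel, an opaque syringe or matched volumes. For context only, protocol v1.0 (section 8.2.3) had "the barrel of the syringe masked using tape to avoid observation of the volume", and told participants the reason was concealment, "as the vaccines will be drawn up into different sized syringes". The change between versions is not the point; the passage shows that masking was thought useful and feasible. The gap lies in the current text.

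**4. How sensitive the planned test would be.** The documents give no reporting gap, so this is an illustration and not an estimate. Assume equal true reaction rates, reporting at rate p1 in one arm and p2 in the other, n = 120 per arm, and a two-sided 5% chi-squared test of one lower dose against full dose. (SAP 5.3.3 does not say whether the test is pairwise.) With p̄ = (p1 + p2)/2,

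P(reject) ≈ Φ{ [ |p1 − p2| − 1.96 √(2p̄(1 − p̄)/n) ] / √[ (p1(1 − p1) + p2(1 − p2))/n ] }.

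For 30% versus 20%: (0.10 − 1.96 × 0.0559)/0.0555 = −0.17, giving 43%.

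| Higher rate | 5-point gap | 10-point gap | 15-point gap |
|---|---|---|---|
| 10% | 31% | – | – |
| 20% | 17% | 58% | – |
| 30% | 14% | 43% | 80% |

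The 10–30% range is from protocol 5.4 and refers to headache, myalgia, malaise and asthenia. It therefore bears on systemic reactions. The documents give no expected rate for local reactions.

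**The case against.** The case for leaving the text alone has substance. A participant sees one injection, has no other to compare it with, and is not told the allocation. Everyone receives the same information on adverse events. The unblinded nurse and pharmacist are kept out of follow-up, and a blinded study doctor records events using CRF questions on specific reactions. Protocol 13.2.3 and SAP 5.3.2 call the adverse-event analysis descriptive, and dose selection in SAP 3.4 starts from seroconversion. These points limit the damage and stand. They do not conceal the syringe, and blinded recording does not correct what a participant chooses to report. SAP 5.3.3 also adds formal tests to the descriptive analysis.

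Four stronger readings are tempting, and the documents do not support them:

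- *Participants can identify their arm.* Full dose and 1000 IU share 0.5 ml. At most, someone in the other two arms may recognise a reduced volume.
- *The comparisons are biased, with the rejection rates above as their error rates.* The reporting gaps have no source, and neither size nor direction can be derived.
- *A volume effect on local reactions would be a false positive.* If less fluid causes fewer local reactions, that is a real difference between the arms as given. It needs correct labelling and is not an error of the test.
- *Participants who guess a low dose will drop out or be vaccinated elsewhere.* Nothing in the documents shows this, and section 10.9 gives the same re-vaccination advice whatever the arm.

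**Conclusion.** The point holds as a gap in the current protocol and SAP. Followed as written, they do not assure participant blinding in the 500 and 250 IU arms, nor in the child study if a fractional-volume dose is chosen. The local and systemic reaction comparisons of those doses with full dose are at risk of reporting bias, of unknown size and direction.

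The 1000 IU versus full dose comparison is little affected because the volumes are equal. The primary endpoint is little affected because PRNT50 is measured by laboratory staff blinded to dose (protocol 11.2). The exposed outcomes are secondary, so this is a change worth making but not a threat to the trial's main conclusion.

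The conclusion rests on two assumptions: that the fractional volumes are roughly proportional to dose, and that no masking is specified in a site procedure outside these documents.

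**What to change.** In protocol 10.6–10.8 and SAP 3.3, require that the syringe barrel be covered with opaque tape, that syringes of different sizes be covered so that they look alike, and that the injection be given out of view of blinded staff. If taping is already site practice, write it in. If it will not be done, describe the trial as observer- and laboratory-blinded.

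A single syringe model for all arms is not needed and could cost measuring precision at the smallest volume.

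In SAP 5.3.3, add a sentence saying that the 500 and 250 IU local-reaction comparisons reflect dose and injected volume together, and that only 1000 IU versus full dose has equal volume.

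The cost is tape, slightly more preparation time and a few sentences of text. Sample size, endpoints and the primary analysis do not change.
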